### Inclusion criteria

The organisations [1] and individual participants [2] selected for the study will meet the following criteria:
ACCHSs that:
(i)Utilise a health care software system with comprehensive electronic health records, such as MMEx or Communicare [32, 33];(ii)Utilise Medical Benefit Scheme (MBS) item 715 [34], which is a population-based health check specifically designed for health promotion, disease prevention and early diagnosis in Aboriginal and Torres Strait Islander populations;(iii)Have GPs and Aboriginal and Torres Strait Islander Health Workers, and/or practice nurses who assist in delivery of health checks;(iv)Participate in CQI [35](v)Can provide at least 55 current Aboriginal and Torres Strait Islander patients who meet the inclusion criteria.Aboriginal and Torres Strait Islander Peoples aged 50 years and over who are active clients (at least three visits in the last 2 years) of the health service. Despite the MBS 715 being available for all ages (with a category specific for 55 years and over), a 50-plus age group was chosen due to high rates of CIND and dementia documented in this group [36] and aligns with the age criteria for access to the Australian Government’s aged care services platform, My Aged Care [37].

### Exclusion criteria

Clients will be excluded from audits in the following cases. If they:
(i)Are severely unwell with high likelihood of death within 6 months;(ii)Have not resided in the area for the last 12 months;(iii)Currently reside in residential care and/or;(iv)Are not active patients of the service as defined by the Royal Australian College of General Practitioners’ definition: having attended no less than three visits to the service in the last 2 years [36].

### Intervention

The implementation strategies for the intervention in each cluster will be determined in collaboration with the AWCs and local service leaders and will include the following elements:
(i)Education sessions, designed in collaboration with ACCHS staff including Aboriginal and Torres Strait Islander Health Workers, nurses and GPs, and provided to the ACCHS staff through a method that supports the needs of the health service. For example, workshops, webinars, online educational modules etc.; depending what the ACCHSs determine is the most effective form of training for their organisation.(ii)Gaps and areas for practice development or learning will be identified with each health service team and organisation, based on results of the medical record audits developed and undertaken specifically for this project, together with feedback from each agency. The research team will engage with existing CQI processes in the health service to reinforce practice change behaviours.(iii)An evidence-based best-practice guide to cognitive impairment and dementia care for older Aboriginal and Torres Strait Islander peoples in primary care will be developed and refined through extensive stakeholder consultation, including a modified Delphi process [38], workshops with the project’s Translation Working Group, and advice from the project’s Aboriginal and Torres Strait Islander Reference Group.(iv)Adaptation and modification of the standard software used by primary care agencies to record and manage client care. The inclusion of prompts, decision support systems and adaptations to templates such as chronic disease care plans and Aboriginal Health Checks, and evidence-based guidance regarding dementia assessment and care will provide practical support for staff on a daily basis.(v)Development of tailored care pathways for individual ACCHSs.

### Outcomes

The *primary outcome* is new documentation of dementia or CIND within healthcare records. This includes: (i) evidence of cognitive screening, and/or (ii) documentation of inquiry into cognitive health (e.g. asking questions regarding memory; obtaining informant report regarding cognition; (iii) laboratory or imaging investigations specifically requested for assessment of dementia. The data informing the primary outcome measure will be collected during regular audit cycles (detailed below), both prior to and during the project implementation phase.

*Secondary outcomes* are focused on improved health and well-being of older Aboriginal and Torres Strait Islander peoples with dementia, their carers and families. This will be measured through two validated quality of life tools in the CGA (refer below).

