**Methods/design:**

The prospective study will use a stepped-wedge cluster randomised controlled trial design working with 12 Aboriginal Community Controlled Health Services (ACCHSs) across four states of Australia. Utilising a co-design approach, health system adaptations will be implemented including (i) development of a best practice guide for cognitive impairment and dementia in Aboriginal and Torres Strait Islander communities (ii) education programs for health professionals supported by local champions and (iii) development of decision support systems for local medical software. In addition, the study will utilise a knowledge translation framework, the Integrated Promoting Action on Research Implementation in Health Services (iPARIHS) Framework, to promote long-term sustainable practice change. Process evaluation will also be undertaken to measure the quality, fidelity and contextual influences on the outcomes of the implementation.

The primary outcome measures will be rates of documentation of dementia and CIND, and evidence of improved management of dementia and CIND among older Indigenous peoples attending Aboriginal and Torres Strait Islander primary care services through health system changes. The secondary outcomes will be improvements to the quality of life of older Indigenous peoples with dementia and CIND, as well as that of their carers and families.

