### Aims, objectives and outcomes of the study

The primary aim is to:

(i) Improve detection and management of dementia and CIND among older Aboriginal and Torres Strait Islander peoples attending primary care services through health system changes that include the following features:
Collaboratively developed education programs delivered for capability building of health practitioners including Aboriginal and Torres Strait Islander Health Workers, nurses and GPs. This program will be supported by local champions.Development of a culturally appropriate Aboriginal and Torres Strait Islander best practice guide (BPG) for dementia and CIND, and;Decision support systems including software modifications and adaptations of the current Aboriginal Health Check (Medical Benefit Scheme (MBS) 715) templates;

The secondary aims include improvement in the quality of life of carers and older people with dementia and CIND.

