### Hypotheses

*Primary hypothesis*: Implementation of the Let’s CHAT Dementia model of care and health system changes will result in an increase in documentation of cognitive assessment and management for dementia and CIND in the clinic population aged 50 and over.

*Secondary hypothesis*: Compared with usual care, implementation of the Let’s CHAT Dementia model of care will: a) improve carers’ quality of life; and b) improve health outcomes and quality of life of those with CIND and dementia and help with health economic evaluation.

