#### Sample size

Previous work in the Kimberley (confirmed by work in NSW) found that in Aboriginal and Torres Strait Islander communities, based on community screening, the true prevalence of dementia in people aged 45 years and over was approximately 10%, and the prevalence for cognitive impairment without dementia was also approximately 10% [5, 45]. Hence, the true prevalence of dementia or cognitive impairment in the relevant population is 20%. In the Kimberley, only 38% of those with dementia and only 3% of those with cognitive impairment had been diagnosed by primary health care practitioners. Moreover, the fraction of dementia cases identified by primary care in this work was likely to be higher than in standard practice as many of those with diagnosed dementia had been identified as part of previous research, with primary care practitioners subsequently notified. Therefore, we assume that no more than 15% of individuals with cognitive impairment or dementia are currently identified by primary health practitioners. The initial prevalence based on detection in primary care will be 15% of 20%, i.e. 3%. At a minimum, the study intervention should enable practitioners to identify at least half (50%) of the primary care patients with dementia or cognitive impairment. This would increase the prevalence based on detection in primary care to 50% of 20%, i.e. 10%. If an intraclass correlation of 0.01 and an average cluster size of 50 individuals is assumed, then the design effect will be 1.49. If the study was an individually randomised trial and we wished to detect an increase in the identification of cognitive impairment and dementia from 3 to 10% then the sample size would need to be at least 388 people (α = 0.05, power = 0.8). Therefore, the sample size required for this cluster randomised study will be 578 (388 × 1.49). Allowing for 10% drop-outs we plan to recruit 12 clusters of at least 55 people each, a total sample size of at least 660 individuals. Secondary outcomes compare the effect of earlier detection on scales of depression and stress and this sample size also has adequate power for these scales. We expect approximately 18 cases to be detected in the control period and 60 in the intervention period. The average cluster size will be 6.5 and assuming an ICC of 0.01, the design effect will be 1.055. Thus, our effective number of control cases will be 17 (18/1.055) and intervention cases 57 (60/1.055). Based on the variation found on the longitudinal data of carer strain in the Kimberley, our proposed study will provide over 80% power to find any clinically important effects.

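### The primary outcome as defined (cognitive screening, inquiry or investigations) is not the event the trial is sized on (identified cases, 3% rising to 10%), so the stated 80% power is unsupported for it

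*Protocol article*

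**What the plan says.** The Outcomes section says that the primary outcome "is new documentation of dementia or CIND within healthcare records". It then says what counts: "This includes: (i) evidence of cognitive screening, and/or (ii) documentation of inquiry into cognitive health", with asking about memory and obtaining an informant report as examples, and, as item (iii), "laboratory or imaging investigations specifically requested for assessment of dementia". A recorded diagnosis or identified case is not among the listed items.

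Other sections describe the target differently:

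- **Aims:** "Improve detection and management of dementia and CIND among older Aboriginal and Torres Strait Islander peoples attending primary care services".
- **Primary hypothesis:** "an increase in documentation of cognitive assessment and management for dementia and CIND", in clinic clients aged 50 and over.
- **Abstract, Methods/design:** the primary outcome measures are "rates of documentation of dementia and CIND, and evidence of improved management of dementia and CIND".
- **Sample size:** the powered quantity is the share of clients whom primary care has identified as having dementia or cognitive impairment. It starts at 15% of a 20% true prevalence, or 3%. Of the intervention the section says "This would increase the prevalence based on detection in primary care to 50% of 20%, i.e. 10" (per cent). It expects about 18 detected cases in the control period and 60 in the intervention period.

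Among the intervention elements is a change to the clinical software: "The inclusion of prompts, decision support systems and adaptations to templates", including the Aboriginal Health Check template.

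**The concern.** The definition and the sample size describe different events. Items (i) to (iii) record that someone looked, whatever was found. A client who is screened and found normal can therefore meet the primary outcome as worded, but is not an identified case in the Sample size section.

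Two things are at stake. The first is the power statement, because the rates and difference behind the 80% were derived for identified cases. The second is interpretation. Prompts and modified templates act directly on the recording of screening and inquiry, so the outcome could rise without any further person being recognised as having dementia or CIND. Such a result would answer the primary hypothesis as far as assessment goes, but not the detection part of the primary aim.

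A smaller inconsistency lies alongside. The abstract and the hypothesis include management in what is primary, and the Outcomes definition does not.

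**Working it through.** **1. Reproduce the plan's figure.** Inputs from Sample size: p1 = 0.03, p2 = 0.10, α = 0.05, power 0.80. Sidedness is not stated; two-sided reproduces. With p̄ = 0.065 and pooled variance under the null:

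n per group = [1.960·√(2·0.065·0.935) + 0.842·√(0.03·0.97 + 0.10·0.90)]² / 0.07² = (0.683 + 0.290)² / 0.0049 = 193.5, rounded up to 194.

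The total is 388, as stated. The design effect is 1 + (50 − 1)·0.01 = 1.49, and 388 × 1.49 = 578, as stated. The calculation is right for identified cases.

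**2. Which event do the 3% and 10% describe?**

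| | Sample size | Outcomes |
|---|---|---|
| Event | Client identified as having dementia or cognitive impairment | Screening, inquiry or investigation recorded |
| Abnormal finding needed? | Yes | No |
| Ceiling | 20% of clients (the assumed true prevalence, if identification is correct) | Up to 100% of clients |
| Usual-care rate | 3% (15% × 20%) | Not given |
| Target rate | 10% (50% × 20%) | Not given |

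The 3% and 10% are fractions of the 20% prevalence. They cannot be carried over to an event that can be recorded for any client in the audit.

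**3. Power for the outcome as defined, under assumed rates.** The document gives no usual-care rate for screening, inquiry or investigations, so 10% to 33% is an assumed range. Its top is the 33% completion of subsidised primary care screening in the Background. That figure concerns health screening in general and is not a rate of cognitive inquiry.

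The plan's own shortcut has 12 × 50 = 600 clients and a design effect of 1.49, split into two equal groups. The effective n per group is 300 / 1.49 = 201.3, and

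power = Φ{ [d·√n − 1.960·√(2p̄(1 − p̄))] / √(p1(1 − p1) + p2(1 − p2)) }, with d = p2 − p1.

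| Control rate | Power, 7-point rise | Power, 15-point rise | Smallest rise with 80% power |
|---|---|---|---|
| 3% (plan, identified cases) | 82% | not applicable | 6.8 points |
| 10% (assumed) | 54% | 98% | 9.9 points |
| 20% (assumed) | 38% | 92% | 12.2 points |
| 33% (assumed) | 31% | 87% | 13.6 points |

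The 7-point column keeps the plan's difference for identified cases, which has no more claim to the composite than the 3% does. The 15-point column is equally an assumption. Together they show that the answer depends on two quantities the document does not give.

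**4. ICC.** The 0.01 is also stated for identified cases. A service-wide recording practice might cluster more. As an illustration only, at an ICC of 0.05 the design effect is 1 + 49·0.05 = 3.45, and power for 20% to 35% falls from 92% to 60%.

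**The case against.** **The list may be additive.** The Outcomes section introduces the items as inclusions, so they may supplement recorded diagnoses and not replace them. The data collection timetable has its own row for documentation of dementia or CIND. That is a fair reading, and it is why the point is put as what can count as an event. It does not remove the mismatch: the outcome would then mix diagnosed cases with clients screened as normal, and its rate would still not be 3% or 10%.

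**A process outcome is legitimate.** In a trial of health-system change, documented assessment is a reasonable target, and the primary hypothesis names it. This stands. It is why keeping the composite remains an acceptable remedy, provided the trial is sized for it and the conclusion is worded to match.

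**The power figures are not this trial's power.** This also stands. They follow the plan's parallel-group shortcut. The 18 and 60 expected cases are 3% and 10% of 600 each, so the plan appears to count about 600 clients in each period, and successive audits are linked. With 600 / 1.49 per condition, ignoring pairing and time trend, a rise from 10% to 17% would have 83% power instead of 54%. The figures show sensitivity to the missing inputs and nothing more.

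**The article condenses a fuller plan.** That would excuse missing detail. Here both the outcome and its sizing are stated, and they refer to different events.

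**Stronger readings.** A reader might infer that the trial is underpowered. The document does not support that: prompts could raise documented screening by much more than 7 points. A reader might also infer that there are four separate primary endpoints. The abstract and the Outcomes section share a label, and the assessment part of the hypothesis fits items (i) to (iii). The real conflicts are two: identified case versus assessment activity, and whether management is primary.

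**Conclusion.** The point holds and should be resolved before the analysis is fixed. The primary outcome in the Outcomes section and the event in the Sample size section are not the same, and reading the listed items as additive does not cure this. That conclusion needs no assumed rate; it follows from setting the two sections side by side.

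The 388 and 578 are correct for identified cases. For the outcome as defined, the 80% is unsupported in an unknown direction: 54% to 31% for a 7-point rise and 98% to 87% for a 15-point rise, over assumed control rates of 10% to 33%, with an ICC of 0.01 and the plan's shortcut.

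A positive primary result would show more documented assessment activity. It would not by itself show better detection. It would be too strong to call such a result uninformative, since the hypothesis asks for more documented assessment. Whether management is part of the primary outcome also needs settling.

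**What to change.** Name one primary outcome and align the abstract, Hypotheses, Outcomes and Sample size sections with it, stating whether management is primary or secondary. There are two ways to do this.

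- **(a) Identified case as primary.** Use a new recorded diagnosis or identified case of dementia or CIND. This keeps the 3% to 10% calculation. Screening, inquiry and investigations become a separate secondary process outcome. The definition should say how cases already on record at baseline are counted, because the 3% is a prevalence of identified cases.
- **(b) Process composite as primary.** Restate its control rate, target difference, ICC and power, for example from the baseline audit, and limit the primary conclusion to assessment activity. Recorded diagnoses then become a secondary outcome that speaks to detection.

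Option (a) fits the existing sample size and the detection aim; option (b) fits the assessment part of the hypothesis. Either one is a formal amendment of the primary outcome or of its justification, and so more than an edit of wording. Neither needs new data collection: under Medical record audit, the tool already records assessments and investigations relating to cognition as well as new diagnoses.

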### Dissemination and translation

Formal feedback of outcomes to health services personnel will occur every 6 months. Regular community updates will be provided through various culturally appropriate media, including newsletters and posters. Two workshops will be held (at baseline and on completion of the project) in each region for consumers, carers, health professionals, aged care workers and all other relevant stakeholders to provide and discuss information, present findings, and to set research priorities for the future. Ongoing translation strategies will be developed in collaboration with AWC and relevant stakeholders.

### Methods: data collection, management and analysis

#### Data collection and management

##### Medical record audit

A specific audit tool has been developed to collect data from eligible ACCHS clients 50 years and over (see Table 2 for data collection timetable). The audit tool documents clients’ dementia risk profile, any assessments or investigations relating to cognition, new diagnoses of dementia and CIND as well as describing the care pathways of any cognitively impaired clients, including referrals, hospitalisations and mortality. Data will be collected by trained research assistants using REDCap; an online, secure, password protected, web-based data collection support tool. Data will be de-identified with a unique identifier code allocated to each participant to enable linking between successive audits, with data re-identifiable only in the clinical setting. Audits will be completed either by trained research assistants or ACCHS staff, depending on each service’s preferences.

### Comprehensive geriatric assessment (CGA) - client

Patients identified with possible dementia or CIND by audit and the gender and age matched case controls will be invited to be participants in the CGA. Different measures will be utilised in the CGA to gather data to assess individual outcomes throughout the life of the study. Cognition, quality of life, chronic pain, continence, daily function, mental health, history of psychosocial stress, nutrition, physical activity, sleep quality, frailty, visual and hearing impairment, muscle mass, blood pressure, grip strength and gait will be assessed (see summary table, Appendix 1, for standardised tools used). The CGA contains a detailed cognitive assessment section which includes the Kimberley Indigenous Cognitive Assessment, the Clock Test, Colour Trail Making Test and the Symbol Digit Modalities Test [39–42]. A semi-structured interview will be used to ascertain demographic factors, preferred language and education. Structured responses will be sought from the participants on the following: medical history, medications, past and present tobacco use (including chewing tobacco), past and present alcohol use, past and present drug use and history of head trauma. The CGA survey information will be collected by trained research assistants and will be entered and stored securely in REDCap. Paper copies will be stored in locked file cabinets in areas accessible by project research team members only.

### Comprehensive geriatric assessment - Carers/ family

Carers and/or family will also be invited to complete a section of the CGA. They will be asked to assess the patient’s health. Frailty, cognition, daily function, mental health, and nutrition will be assessed. In addition, a semi-structured interview will be used to ascertain both past and present smoking (including chewing tobacco), alcohol, and drug use by the patient from the carer and/or family member’s perspective. Different measures will also be utilised to assess the carer’s and/or family member’s health, including a carer burden interview, a mental health assessment and a quality of life test. Individual and carer/family assessments will be completed by trained research assistants. The CGAs will be reviewed by geriatrician who will make care recommendations regarding clinical management and care which will be fed back to ACCHSs.

### Data collection timetable

Table 2. Data collection timetable

**Table Taba:** 

Data collection	Baseline	6 monthly^a^	12 monthly^a^
Audit tool: demographic data & dementia mapping	X	X	X
Documentation of dementia or CIND (audit tool)	X	X	X
Audit documenting best practice	X	X	X
Participant: Comprehensive Geriatric Assessment	X		X
Carer: Outcomes	X		X
Health professionals: Process data	X	X	X

^a^6 monthly collection of data will continue from baseline to 36 months

